**Methods/design:**

This will be a three-armed randomized control trial (RCT) including pre/post intervention and follow-up. The trial will include 90 older people with hip fractures who will be randomly assigned to a telerehabilitation group (*N* = 30), face-to-face visits (N = 30) and a control group. The aim of the intervention is to improve the transition from rehabilitation units to community dwelling. It will include 10 videoconferencing/ face-to-face sessions from an occupational therapist in the presence of the primary caregiver. Each session will be utilized to guide the participants to achieve their self-identified goals, focusing on problem-solving for daily life situations and on the ability to implement the discussed strategies for a variety of activities. Outcome measures include Functional Independence Measure (FIM) for evaluation of ADL, SF-12 for evaluation of Health-related QOL, The Geriatric Depression Scale (GDS) and The Zarit Caregiver Burden Scale. Data will be analyzed using Repeated measures MANOVA.

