## Background

Hip fracture is one of the most serious osteoporotic fracture, and the second most common cause of hospitalization among the age group older than 65 years [1]. Hip fractures occur predominantly in the geriatric population [2, 3], due to higher rates of osteoporosis and falls [4]. The lifetime risk of hip fracture is 9% for women and 4% for men [5]. Hip fractures are a major public health problem in terms of patient morbidity, mortality and costs to health and social care [4, 6]. With an ageing population, and a growing proportion of people aged 80 years or older, the societal and economic burden of osteoporosis-related fractures is deemed to be increasing [7]. The healthcare costs for hip fractures are the highest (€20,000/patient) in comparison with other costs of injuries [8]. Osteoporotic hip fractures incur a high economic cost mainly due to the first hospitalization [8], but also due to subsequent outpatient visits, home care [6] and complications following initial hospital discharge [4, 9]. Therefore, further research is needed to identify the most effective and cost-effective rehabilitation pathways for these patients [10].

A third of older adults with hip fracture will be readmitted to hospital within 30 days of their return home [11], and up to 20% of patients die in the first year following hip fracture [12]. Hip fractures have profound effects on quality of life (QoL) and activities of daily living (ADL) [13, 14]. Most patients surviving hip fracture experience reduced mobility, lose their functional ability [15] and independence [16], and suffer from depression [17]. A systematic review found that after 1 year, 29% of hip-fracture patients did not reach their pre-fracture level of ADL, and 35% were not able to walk independently [2].

Hip fractures nearly always necessitate hospitalization and rehabilitation [18, 19]. Rehabilitation is a significant factor impacting the level of functional independence following hip fracture [20]. In the United States, more than 90% of Medicare beneficiaries utilize post-acute-care rehabilitation after an acute hip fracture hospitalization [21]. In Israel, 73.5% of the hip-fracture patients received inpatient rehabilitation, 14.3% received ambulatory rehabilitation treatment without an inpatient phase, and 12.2% received no rehabilitation [22].

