### Trial design, randomization and recruitment

This study is a three-armed, evaluator-blind, randomized control trial (RCT) and will be implemented according to CONSORT guidelines [57]. Participants will be assigned to research and control groups by using a blocked randomized controlled design, stratified based on age. The randomization sequence will be computer generated and will be known only to the responsible investigator.

All participants will be recruited at the time of discharge from hospital. Health professionals employed at the hospital will screen and refer to a research assistant the interested clients who meet the inclusion criteria. The research assistant will obtain informed consent from caregivers and patients prior to randomization and trial inclusion. Participants (*n* = 90) will be randomized after baseline assessment in the three-arm study. The rehabilitation program will be identical in both intervention groups; only the delivery mode will differ: in-home telerehabilitation or face-to-face home visit. The patients allocated to all groups will continue to receive the standard usual care to improve adherence to intervention protocols. All outcomes will be measured at all three time points: Baseline-pretest (T0), immediately following intervention (post intervention 10 weeks) (T1), and a 6-month follow-up (T2) (See Fig. 1).

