### Data analysis

Quantitative data will be analyzed using SPSS 21.0. Descriptive statistics will be obtained on the demographic, social and clinical pretest characteristics of subjects in the three groups. Differences in these variables between the intervention and control groups will be examined using either chi-square tests or analysis of variance. Feasibility in the research groups will be calculated according to the of participants who complete the trial.

Repeated-measures MANOVA will be used to test the effects of the group assignments (intervention vs. control), the effects of time (baseline, post-intervention, and 6-month follow-up), and the group-by-time interaction for measuring all the outcomes. Repeated-measures MANOVA is recommended as being straightforward, powerful, and appropriate to treatment outcome investigations [79]. In addition to providing a multivariate analysis of the effect of treatment on the combined changes in all measures and healthcare costs, this approach also provides a univariate analysis of the effect of treatment on each measure, thus allowing an investigation of which measures were most affected by treatment [79]. *p*-Values less than 0.05 are considered to be statistically significant in all comparisons.

All qualitative interviews (patients and caregivers) will be video/audio-recorded and transcribed. Conventional content analysis with constant comparative methods will be used for coding and analysis. All data will be collected anonymously, and access will be restricted to the investigators.

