### Sample size calculation

The sample size was based on RCT that compared the effectiveness of face-to-face home rehabilitation to conventional care after hip fracture of geriatric patients [64]. The home rehabilitation group showed a higher degree of recovery in self-care using the FIM, (calculated effect size: d = 0.8). The minimum sample size at the significance level of 5% (one-sided test) and power of 80% is 25 in each group. Estimated drop-out rate is 20%; therefore, a maximum of 30 participants will be recruited for each group.

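### One repeated-measures MANOVA over all outcomes and visits drops every participant with an incomplete record, which costs precision and risks bias when 20% dropout is expected

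*Protocol article*

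**What the plan says.** The Data analysis section of the protocol article names repeated-measures MANOVA in SPSS 21.0, with group, time (baseline, post-intervention, 6-month follow-up) and their interaction, for all outcomes. It wants one multivariate test on the changes in every measure together with healthcare costs, and takes the univariate result for each measure from the same approach. It defends the choice: "Repeated-measures MANOVA is recommended as being straightforward, powerful, and appropriate to treatment outcome investigations". Age does not appear in the model described.

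Three other places bear on this choice:

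- Sample size calculation: "Estimated drop-out rate is 20%; therefore, a maximum of 30 participants will be recruited for each group".
- Trial design, randomization and recruitment: participants are allocated "by using a blocked randomized controlled design, stratified based on age", and all outcomes are measured at T0, T1 and T2.
- Outcome measures: FIM, two SF-12 summary scores, GDS, COPM performance and satisfaction, and the caregiver's Zarit interview. That is seven scores from two respondents. The post-intervention and follow-up assessments are done by e-mail or phone.

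**The concern.** Classical repeated-measures MANOVA works on a complete vector. Here the vector holds seven scores plus costs, over three visits. One gap removes the participant from the joint test and from the univariate tests that come out of the same fit. A missing caregiver form therefore removes the patient's FIM, and a missed T2 removes a T1 score that was collected.

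Three things are at stake:

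- **Discarded data.** Partial records are thrown away in a trial of 30 per arm.
- **A completer comparison.** The analysis rests on those who finished. If the people lost differ in outcome, and differ between arms, the comparison is no longer the randomised one.
- **Unused information.** T0 enters as a further response and not as a covariate, and the factor used to stratify randomisation is not in the model.

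**Working it through.** **Inputs from the protocol article.** "The trial will include 90 older people with hip fractures" in three arms; "calculated effect size: d = 0.8"; 30 per arm; 20% dropout; "The minimum sample size at the significance level of 5% (one-sided test) and power of 80% is 25 in each group". Visit correlations, loss mechanisms and extra missingness rates are not given, so those used below are assumptions.

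**1. The plan's own figure.** The normal formula is n = 2(z_α + z_β)²/d².

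- One-sided 5%: 2 × (1.645 + 0.842)²/0.64 = 19.3, so 20 per group (21 with the t distribution).
- Two-sided 5%: 2 × (1.960 + 0.842)²/0.64 = 24.5, so 25 per group (26 with t).

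The stated 25 matches the two-sided normal formula and not the one-sided test named. That is a separate matter, but it is why power is shown both ways in step 3.

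**2. Loss from dropout alone.** 30 × 0.8 = 24 per arm, or 72 of 90.

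**3. Cost at T1 if the 20% are lost after T1.** A model using all available data keeps 30 per arm at T1; the MANOVA keeps 24. The standard error ratio is √(30/24) = 1.118, about 12% larger. For a simple two-group t test at d = 0.8:

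| | 24 per arm | 30 per arm |
|---|---|---|
| Two-sided 5% | 77.4% | 86.1% |
| One-sided 5% | 86.1% | 92.2% |

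**4. Scattered gaps on top of dropout.** With missingness m, over seven scores at two post-baseline visits:

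| m (assumed) | Each score independently: 72(1−m)^14 | Whole visits: 72(1−m)^2 |
|---|---|---|
| 2% | 54 | 69 |
| 5% | 35 | 65 |

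**5. Precision at T2, and bias.** A simulation used two arms of 30, three visits, a true effect of 0.8 SD at T1 and T2, and 6,000 runs. The T0–T1, T0–T2 and T1–T2 correlations were either all 0.5, or 0.5, 0.35 and 0.7. It compared change from T0 in complete cases with a likelihood-type estimator using all available data. Loss fell between T1 and T2.

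| Loss mechanism | Complete-case bias, T1 (SD) | Complete-case bias, T2 (SD) |
|---|---|---|
| Completely at random, 20% | about 0 | about 0 |
| Depends on T1, same in both arms | about 0 | about 0 |
| Depends on T1, 30% control vs 11% intervention | −0.11 | −0.01 to −0.05 |
| Depends on T1, opposite direction by arm | −0.23 to −0.24 | 0 to −0.10 |

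The all-available-data estimator stayed within 0.01 SD throughout. Every mechanism here is missing at random given T1, which favours that estimator. Under loss completely at random, the complete-case T2 standard error was 0.286/0.279 = 1.025 to 0.335/0.314 = 1.067 times the other. Under the T1-dependent mechanisms it ran from about 2% smaller to 4% larger.

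**6. T0 as covariate.** With equal SDs at T0 and follow-up, the variance relative to change from T0 is (1−ρ²)/[2(1−ρ)] = (1+ρ)/2. That is 35%, 25% or 15% lower at ρ = 0.3, 0.5 or 0.7. If the T0 SD is half the follow-up SD, the ratio is (1−ρ²)/(1.25−ρ), which is only 4%, 0% or 7% lower. The second case matters for FIM: entry requires a discharge score above 90 on a scale ending at 126, so the baseline spread is cut.

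**7. Age stratum.** For an age–outcome correlation r, omitting age multiplies the standard error by 1/√(1−r²): 1.005 at r = 0.1 and 1.091 at r = 0.4.

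**The case against.** The strongest reply is that this is a condensed article. It does not state complete-case handling or forbid imputation or covariates, and the full analysis plan is not shown. That is fair as far as silence goes. But the article does fix the method, its joint scope and its three occasions, and complete-record handling follows from that method unless something overrides it. Imputation would repair the listwise loss; it would not change the use of T0 as a response.

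A reader might infer more than the document supports:

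- **That the estimates will be biased.** Bias was about zero under loss completely at random, and also when loss depended on outcome in the same way in both arms. The article does not say that loss will differ by arm.
- **That omitting age, or using T0 as an occasion, biases the comparison.** Neither does. The group-by-time interaction is a valid comparison of change under randomisation.
- **That controls have no contact and so drop out differently.** The Control group section gives them usual care and rehabilitation, and they are assessed at every visit. They lack study therapy only.
- **That high mortality makes informative loss certain.** The Background says "up to 20% of patients die in the first year following hip fracture", but of hip-fracture patients in general. This trial enrols people going home with FIM above 90, and its last visit is at 6 months.
- **That the analysed set will fall to 54 or 35.** Those figures need independent gaps in 14 scores. E-mail or phone assessments may well be missed whole, which gives 69 or 65.
- **That adjusting for T0 brings a sure gain in power.** It depends on equal SDs, which is doubtful for FIM.

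It also stands that a mixed model with T1 and T2 as responses recovers nothing for anyone lost before T1, and does not settle how deaths should be treated.

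**Conclusion.** The concern holds in a limited form. The stated method suits a trial that expects 20% dropout poorly, because one missing score removes a participant from every outcome.

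The firmest cost is at T1: a standard error about 12% larger if the 20% are lost after T1, and no recoverable loss if they all leave before it. At T2 the cost is modest: about 2.5% to 7% under loss completely at random, and close to nil under some other mechanisms. Scattered missing forms would add to this by an amount the document does not allow one to fix.

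Bias is conditional on loss that is both outcome-related and different by arm. The simulated values, up to about a quarter of an SD at T1, illustrate such mechanisms and are not predictions. T0 as an occasion and the missing age term are questions of efficiency: a variance factor of (1+ρ)/2 for T0 at best, possibly near no gain for FIM, and 0.5% to 9% in standard error for age over the assumed correlations.

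This should be changed, but it does not invalidate the trial.

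**What to change.** Replace the MANOVA by a linear mixed model for each outcome:

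- responses at T1 and T2;
- fixed effects for arm (three levels), visit, arm-by-visit, the T0 value and the age stratum;
- unstructured within-person covariance;
- all randomised participants with any post-baseline value, in the arm assigned.

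Report deaths and losses by arm, and add one sensitivity analysis for data not missing at random.

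The cost is small. The model runs in the SPSS already planned and needs no further participants; beyond the wording there is the reporting of losses and one extra analysis. The joint multivariate test is given up. The model assumes data missing at random, which is weaker than what a complete-case analysis needs but still an assumption. Participants lost before T1 still contribute nothing.

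### The univariate follow-up tests are credited with showing which measures were most affected, but tests of each measure against zero do not compare measures

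*Protocol article*

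**What the plan says.** The Data analysis section plans a repeated-measures MANOVA with group, time and group-by-time effects for all outcomes. It gives two products of this method. The first is "a multivariate analysis of the effect of treatment on the combined changes in all measures and healthcare costs". The second is described in these words: "this approach also provides a univariate analysis of the effect of treatment on each measure", followed directly by "thus allowing an investigation of which measures were most affected by treatment". The threshold is the same throughout: p-values "less than 0.05 are considered to be statistically significant in all comparisons".

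The Outcome measures section lists the FIM (18–126), the SF-12 with physical and mental summaries, the GDS (0–15, higher is worse), the COPM (performance and satisfaction, each 1–10) and the Zarit interview (0–88, higher is worse, concerning the caregiver). That makes five instruments, or seven scores if both SF-12 summaries and both COPM ratings are counted. The article names no contrast between measures, no common scale and no interval for a difference between effects.

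**The concern.** The sentence moves from a separate analysis of each measure to a statement about which measures responded most. The first does not deliver the second. If FIM reaches p < 0.05 and GDS does not, this shows that an effect on FIM was detected and that one on GDS was not. It does not show that FIM was affected more. For that, the difference between the two effects must itself be estimated, on a common scale.

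The problem is separate from type I error. With every p-value adjusted for multiplicity, significant on one measure and not on another would still be no evidence of a difference between them. Comparing raw effects does not help, because a point on the FIM and a point on the GDS are different quantities and the scales do not all run in the same direction.

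At stake is how the secondary results are read. Chance variation between outcomes could be taken for a real pattern across daily function, quality of life, depression and caregiver burden.

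**Working it through.** **Inputs from the protocol article.** Sample size calculation: 25 per group, "calculated effect size: d = 0.8" (FIM self-care). Data analysis: 0.05 for every comparison.

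**Assumptions not in the article.** Both outcomes have the same true standardised effect; the correlation between outcomes is 0.3 to 0.5; d = 0.5 serves as a second, smaller effect; outcomes are normal; each is tested by a two-sided, two-arm t-test.

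**The stated sample size.** Two-sided 5%: 2 × (1.960 + 0.842)² / 0.8² = 24.5, so 25. One-sided 5%: 2 × (1.645 + 0.842)² / 0.8² = 19.3, so 20. The 25 therefore matches a two-sided test, although the article labels it one-sided. That is a separate matter; here 25 is only the number analysed per arm, and the two-sided test is the one under which it gives about 79% power (t-test).

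**Chance of a split verdict.** For two outcomes with equal effects,

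P(exactly one significant) = 2 × [P(one significant) − P(both significant)].

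Simulated at 25 per arm (40,000 trials per row):

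| True d, both outcomes | Correlation | P(one significant) | P(both significant) | Split |
|---|---|---|---|---|
| 0.8 | 0.3 | 0.793 | 0.654 | 2 × 0.139 = 0.28 |
| 0.8 | 0.5 | 0.793 | 0.676 | 2 × 0.117 = 0.23 |
| 0.5 | 0.3 | 0.411 | 0.215 | 2 × 0.196 = 0.39 |
| 0.5 | 0.5 | 0.410 | 0.246 | 2 × 0.164 = 0.33 |

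Separate runs of the same setting gave 0.24 in the second row, so the ranges are about 24–28% and 33–39%. With 30 per arm and no dropout, the split at d = 0.8 falls to about 17–20%.

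**Does ranking by observed effect size avoid this?** No. With five equally affected outcomes at 25 per arm, d = 0.8 and correlation 0.3 to 0.5, the median gap between the largest and smallest observed effect is 0.49 to 0.57 SD.

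**Precision of a direct comparison.** The standard error of one standardised difference is about √(2/25) = 0.283. For the difference of two it is about 0.283 × √(2(1 − r)): 0.335 at r = 0.3 and 0.283 at r = 0.5. The unadjusted 95% half-width is then 1.96 × 0.335 = 0.66 or 1.96 × 0.283 = 0.55 SD. Two effects would have to differ by more than half an SD before even one unadjusted pair was separated.

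**Sensitivity to the planned test.** I repeated the exercise with a univariate three-arm group-by-time F test, 25 per arm, both intervention arms equally effective at T1 and T2, and an assumed within-person correlation of 0.6. A pair splits in about 10–12% of trials at d = 0.8 (power about 93%) and in about 36–41% at d = 0.5 (power about 52%). The rate depends strongly on the true effect and on the test.

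**Why a direct comparison needs simultaneous intervals.** Seven scores give 7 × 6 / 2 = 21 pairs. If all seven are equally affected and each pair is judged by its own unadjusted 95% CI, at least one false difference appears in about 44% of trials (studentized range for seven means at 1.96 × √2), for one arm contrast at one time point.

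**The case against.** The strongest reply is that the clause explains why MANOVA was chosen and is not a decision rule. It speaks of an investigation, and it can be read as the usual follow-up to an omnibus test: look at which outcomes show the effect. This largely stands. A reader might infer that the plan will rank outcomes by significant versus non-significant, or that the trial will report that the programme acts on some domains more than others. The article says neither. It sets no ranking procedure and proposes no comparison of raw effects, and its Discussion makes no claim about which domain benefits most.

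A reader might also infer that the trial's main conclusions are compromised. They are not. Study aims lists effectiveness against standard care, maintenance, cost-effectiveness and user experience; none requires comparing one outcome with another, and the group-by-time test is untouched.

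It is also fair that an article may leave standardised effects and intervals to a fuller document. The point therefore does not rest on their absence. It rests on the inference the article does state, which is not valid whatever the fuller document holds. Nor does the purely descriptive reading rescue the words most affected, since observed effect sizes at this sample size order equally affected outcomes largely by chance.

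Finally, the split rate is partly generic: two independent tests with 79% power each disagree in 2 × 0.79 × 0.21 = 33% of trials in any study. The figures illustrate why the inference fails; they do not measure a defect peculiar to this trial.

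**Conclusion.** The point holds as a limited one. The Data analysis section credits the univariate analyses with something they cannot show, and the measures share no scale on which raw effects could be ordered. The consequence is confined to secondary interpretation.

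The split rates of about 24–28% (d = 0.8) and 33–39% (d = 0.5) rest on equal true effects, an assumed correlation of 0.3 to 0.5 and a two-arm t-test. Only d = 0.8 comes from the article, and there it belongs to FIM self-care in one earlier trial; the article gives no effect size for the other measures. The three-arm check shows that the rate can be well below the t-test figure at d = 0.8 and about the same at d = 0.5. The logical point depends on none of these figures.

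**What to change.** Replace the clause with a statement that the univariate analyses show on which measures an effect was detected and do not rank the measures.

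For each measure, report the between-arm difference at T1 and T2 in baseline-SD units, signed so that higher is better, with a 95% CI. State that one measure was more affected than another only if a simultaneous CI for the difference of their standardised effects excludes zero. The interval should be adjusted over all pairs examined, for example by a max-t bootstrap that resamples participants, with each caregiver's score kept with its patient. Label any other comparison between measures descriptive.

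The cost is a change of wording and a bootstrap on data already being collected; no visit, measure or participant is added. There are two downsides. With half-widths above half an SD even before adjustment, the trial will usually be unable to rank its measures. And baseline-SD units depend on who was enrolled: entry requires FIM above 90, which narrows the baseline FIM spread and can enlarge its standardised effect, so that dependence should be noted beside the results.

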### Outcome measures

#### Functional Independence Measure (FIM) [71]

The aim of the FIM is to monitor the recovery of functional ability by people undergoing rehabilitation. The FIM is comprised of 18 parameters, each rated on a scale of 1–7 (range = 18–126) according to the degree of assistance required to perform a specific activity.

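### With no primary outcome and 0.05 applied to every test, the 5% level is not controlled across outcomes, and the 80% power covers only one FIM contrast that the analysis does not single out

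*Protocol article*

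**What the plan says.** **Analysis.** The Data analysis section of the protocol article applies repeated-measures MANOVA to group, time and group-by-time effects for all outcomes. The joint test covers all measures plus healthcare costs. The section adds that "this approach also provides a univariate analysis of the effect of treatment on each measure", so that the measures most affected can be identified. Its decision rule for p-values is: "Values less than 0.05 are considered to be statistically significant in all comparisons". No adjustment is stated.

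**Outcomes.** The Outcome measures section lists FIM, SF-12 (two summary scores), GDS, COPM (performance and satisfaction) and ZBI without ranking them. The Trial design section has all of them measured at T0, T1 and T2. The Study aims section gives a primary aim of effectiveness, tied to no outcome. It makes maintenance after completion a secondary aim, which hints at T1, but the analysis section does not carry that order through.

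**Sample size.** The source is a trial that "compared the effectiveness of face-to-face home rehabilitation to conventional care after hip fracture of geriatric patients". In it, "The home rehabilitation group showed a higher degree of recovery in self-care using the FIM" ("calculated effect size: d = 0.8"). The result is: "The minimum sample size at the significance level of 5% (one-sided test) and power of 80% is 25 in each group". On attrition: "Estimated drop-out rate is 20%; therefore, a maximum of 30 participants will be recruited for each group".

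**The concern.** The sample size section treats one FIM contrast as decisive, whereas the analysis section makes every outcome decisive at the same level. Two things follow.

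- **Error rate.** With several separate tests at 0.05 and none ranked first, a significant result on any score can be read as evidence that the programme works. The chance that this happens with no true effect is well above 5%.
- **Power.** A reader will attach the stated 80% to the planned analysis, but it was derived for one outcome and two groups. It says nothing about the joint test or about SF-12, GDS, COPM, ZBI or costs.

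The Discussion section intends the results to guide practice if the programme is efficacious. Which result would establish efficacy should therefore be fixed before the data are seen.

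**Working it through.** **1. The plan's own figure.** The normal-approximation formula is n per group = 2(z_α + z_β)² / d², with d = 0.8 and z_β = 0.842.
- Two-sided 5%: 2(1.960 + 0.842)² / 0.64 = 24.5, so 25. This reproduces the stated 25 (26 by the t distribution).
- One-sided 5%: 2(1.645 + 0.842)² / 0.64 = 19.3, so 20 (21 by t). The stated 25 is a two-sided number with a one-sided label. That is a separate matter.
- Recruiting 30 with 20% drop-out leaves 30 × 0.8 = 24 completers, which is used below.

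**2. Power of the sized contrast.** The noncentrality is d√(n/2) = 0.8 × √12 = 2.77, with 46 df. Two-sided power at 0.05 is 77.4% (79.1% at 25 per group). One-sided it is 86.1%. Unadjusted testing of further outcomes does not lower these figures.

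**3. Number of scores.** The five instruments give 5. Counting both SF-12 summaries and both COPM ratings gives 7. Adding healthcare costs gives 8.

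**4. False positives across the separate tests.** Assumptions: no true effect, one three-arm F test per score at 0.05, 24 per arm, univariate tests not conditional on the joint test. For independent scores the chance of at least one is 1 − 0.95^k. For equally correlated scores it is simulated; the correlations are assumed, as the article gives none.

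| Scores | 1 − 0.95^k | corr. 0.3 | corr. 0.5 | corr. 0.7 |
|---|---|---|---|---|
| 5 | 22.6% | 21% | 19% | 15% |
| 7 | 30.2% | 28% | 24% | 19% |
| 8 | 33.7% | 30% | 26% | 20% |

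The simulated entries can move by about one point between runs.

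**5. Power of the joint test if only FIM moves.** Simulated group-by-time MANOVA (Pillai's trace) on two change scores per outcome. Settings: three arms of 24, correlation 0.5 between visits within an outcome, and FIM differing by 0.8 SD between usual care and both interventions at T1 and T2.

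| Outcomes | corr. 0 | corr. 0.3 | corr. 0.5 |
|---|---|---|---|
| FIM alone | 82% to 84% | – | – |
| 7 | 33% to 35% | 46% | 61% to 63% |
| 8 | 31% | 40% to 41% | 58% |

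A two-group Hotelling T² test at 24 per group points the same way: 38% to 65% with 8 measures and 48% to 74% with 5.

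**6. Sensitivity to the response pattern.** With 7 outcomes, if FIM moves 0.8 SD and the other six move 0.5 SD, joint power is about 92% at correlation 0 and about 35% at correlation 0.5. The joint test's power therefore depends on inputs that the article does not give.

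**The case against.** - **The primary outcome may be named elsewhere.** A condensed article can leave detail to an analysis plan. But this article states the decision rule outright, for all comparisons, and a later plan that adjusted for multiplicity would contradict it.
- **The two consequences belong to different readings.** If the univariate tests are interpreted only after a significant joint test, the chance of any false claim under no effect is held near 5%, and the joint test's power matters. If they stand alone, the inflation in step 4 applies, but FIM keeps its own 0.05 test and its 77% power. This objection stands: the worst figures from both readings must not be added together. The wording leans towards separate tests without fixing it. Gating would in any case protect only when no outcome is affected; once one truly moves, the others can still be falsely claimed.
- **A reader might infer that neither the 80% power nor any 5% error rate survives.** That goes too far. The sized FIM contrast roughly keeps its power, and the joint test on its own keeps its 5%.
- **A reader might count every pair of arms at every visit** and arrive at a far higher error rate. The Data analysis section specifies no pairwise arm tests and no single-visit tests, so that count is not the plan's rule.
- **A reader might infer that the FIM variable analysed is not the one sized**, because the instrument section says "The FIM is comprised of 18 parameters, each rated on a scale of 1–7" while the sizing refers to self-care. That section describes the instrument. It does not say that only the total will be analysed, so a mismatch is not shown.
- **The joint-power range assumes that only FIM responds.** This is correct; step 6 shows how far other patterns move it.

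**Conclusion.** The point holds in two limited parts.

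1. **Error rate.** No outcome is ranked first, and 0.05 applies to each test. The 5% level is therefore not controlled across the univariate tests: roughly 15% to 34% for at least one false positive. This assumes 5 to 8 scores, between-outcome correlation from 0.7 down to 0, 24 per arm, and no gating by the joint test. No combination examined brings it back to 5%.
2. **Power.** The stated 80% describes one two-group FIM contrast and is roughly right for it. It is not the power of the joint test, which is about 30% to 63% with 7 or 8 outcomes if FIM alone moves, and higher or lower under other patterns. For the remaining outcomes no power is stated.

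This is more than missing detail, because the rule as written leaves no identifiable confirmatory hypothesis. It cannot be credibly repaired once results by arm are known.

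**What to change.** Change the Data analysis and Sample size sections, and the analysis plan to match:

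- Name one primary outcome and time: the FIM score from which d = 0.8 was calculated, stated explicitly, at T1. This fits the Study aims, where maintenance is already secondary.
- Test each intervention against usual care, adjusting for baseline FIM, with Holm control across the two contrasts at an overall two-sided 5%.
- Treat all other outcomes, and T2, as secondary. Report estimates with 95% confidence intervals and no significance claim, or Holm-adjusted p-values.
- Do not use the omnibus MANOVA as the decision test.

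**Cost.** The change is one of wording, but it has a price in power. At the first Holm step (two-sided 0.025), power for d = 0.8 at 24 per arm is 67.5% without baseline adjustment. If d is scaled by the SD of the outcome and baseline correlates ρ with it, the effective d is 0.8/√(1 − ρ²). At ρ = 0.5 this is 0.924 and power is 80.8%. At ρ = 0.3 it is 0.839 and power is about 72%. Entry is restricted to FIM above 90 on a scale ending at 126, so ρ may be below 0.5. The stated power should be restated with its assumed ρ.

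A Bonferroni split over all five instruments would cost more: alpha 0.01 gives 54% power at 24 per arm, and 80% would need 39 completers per arm. A single primary outcome is therefore the cheaper route.
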